### **8.3 Health economic analysis**

The economic evaluation would adhere, as far as possible, to the most up to date NICE Guide to the Methods of Technology Appraisal (36) to ensure that trial findings are informative for national-level policy considerations. The perspective will be limited to NHS secondary care, which will likely cover the main drivers of total care costs, including the initial hospital admission (including the treatment of complications) and subsequent hospital (re)admissions during the 90-days and, separately, during one year from randomisation. NELA/eCRF will provide all relevant individual-level resource use information related to the initial hospital admission, including that related to implementation of the intervention. Electronic hospital resource use data (including inpatient, outpatient and critical care episodes) will be obtained from NHS Digital (or devolved nation equivalents) for the one-year period post-randomisation to estimate total secondary care cost over the 90-day and one year follow-up period. In addition, hospital data covering a period of 90 days pre-randomisation will be retrospectively obtained from NHS Digital (or equivalent) in order to carry out adjustments for baseline differences in mean cost between comparison groups.

Unit costs for each assessed resource use item will be collated from national sources (such as the NHS Reference Costs) where possible; adjustments and additional estimates will be obtained from published studies and expert opinion where needed. These will be applied to individual-level resource use to estimate individual-level costs.

Due to the lack of direct patient assessments in this trial, quality-adjusted life years (QALYs) will be estimated from EQ5D-3L assessments in the EPOCH trial (37) using a mapping approach relevant to the available data (to be determined and established prior to the health economics analysis plan being signed off). Broadly, this will involve estimating an EQ-5D-3L or tariff prediction model in the EPOCH data using relevant patient characteristics common to both studies, and applying that model to our study data to predict EQ-5D-3L or tariff values.

The comparison of resulting QALYs and costs will broadly follow the outcomes analyses (e.g. same comparison groups, intention-to-treat basis, adjustment for minimisation factors and other pre-specified

covariates) and bootstrapped regression approaches (5000 replications) will be used to evaluate uncertainty in the results.

The economic analyses will include cost-effectiveness analyses, measured in terms of incremental cost per DAQH at 90 days (DAQH-90) and incremental cost per QALY gained at two time periods of follow-up: at 90 days and at one year post randomisation. Incremental cost-effectiveness ratios will be reported.

Uncertainty around the cost-effectiveness ratios will be analysed using a bootstrap approach (5000 replications) and summarised using cost-effectiveness planes and cost-effectiveness acceptability curves (CEACs) over a range of relevant values that decision-makers may place upon outcome improvements ( $\lambda$ ). (For QALYs the range is likely to be £0 to £50,000 to include the current value placed on QALY gains in decision-making by NICE). For each value of  $\lambda$ , the proportion of iterations indicating a higher net benefit for the intervention arm will be calculated and plotted as a CEAC.

Sensitivity analyses will be used to examine the effect of analytic assumptions on the results of the cost-effectiveness and cost-utility analyses. This will include the unit costs used to value intervention cost. All cost, outcome and unit cost data used for the economic evaluation will also be presented in a disaggregated format to facilitate interpretations from alternative perspectives.

A health economics analysis plan, specifying in detail the health economics analyses, will be finalised and signed off prior to unblinding the team analysing the study. Longer-term extrapolation will be considered in case of remaining policy uncertainty (e.g. evidence for survival benefit but unclear cost-effectiveness within one year post randomisation), to project survival of participants and evaluate the cost-effectiveness of cardiac output-guided fluid therapy over a longer time period.

#### **8.4 Secondary studies**

The use of FLO-ELA trial data for further secondary studies is encouraged. A prospective statistical analysis plan will be prepared for each secondary study before data analysis commences.

### **9 RESEARCH ETHICS**

The PI will ensure that this trial is conducted in accordance with the Principles of the Declaration of Helsinki as amended in Tokyo (1975), Venice (1983), Hong Kong (1989), South Africa (1996), Edinburgh (2000), Washington DC (2002), Tokyo (2004), Seoul (2008) and Fortaleza (2013) as described at the following internet site: <http://www.wma.net/en/30publications/10policies/b3/index.html>. The trial will fully adhere to the principles outlined in the Guidelines for Good Clinical Practice ICH Tripartite Guideline (January 1997) and to the Mental Capacity Act 2005. The study will be carried out in accordance with the ethical principles in the Research Governance Framework for Health and Social Care, Second Edition, 2005 and its FLO-ELA protocol v5.0

14 November 2024

subsequent amendments as applicable and applicable legal and regulatory requirements. At sites, all accompanying material given to a potential participant will have undergone an independent Research Ethics Committee review. Full approval by the Research Ethics Committee will be obtained prior to starting the trial and fully documented by letter to the Chief Investigator naming the trial site, local PI (who may also be the Chief Investigator) and the date on which the ethics committee deemed the trial as permissible at that site. All members of the trial steering committee will declare conflicts of interest before joining the study group. These will be listed on any publications arising from the trial.

## **10 DATA HANDLING AND RECORD KEEPING**

### **10.1 Confidentiality**

Information related to participants will be kept confidential and managed in accordance with the Data Protection Act (UK), NHS Caldicott Principles (UK), The Research Governance Framework for Health and Social Care (UK), and the conditions of Research Ethics Committee Approval, or corresponding legislation or approvals for a particular participating site. The patient's NHS Number, gender, date of birth and postcode will be collected at randomisation to allow tracing through national records. The personal data recorded on all documents will be regarded as confidential. The PI must maintain in strict confidence trial documents, which are to be held in the local hospital (e.g. patients' written consent forms). The PI must ensure the patient's confidentiality is maintained at all times. The Sponsor will ensure that all participating partner organisations will maintain the confidentiality of all subject data and will not reproduce or disclose any information by which subjects could be identified, other than reporting of serious adverse events. Representatives of the trial management team will require access to patient notes for quality assurance purposes and source data verification, but patients should be reassured that their confidentiality will be respected at all times. In the case of special problems and/or competent authority queries, it is also necessary to have access to the complete trial records, provided that patient confidentiality is protected.

### **10.2 Data storage**

Data will be entered directly on to the secure NELA data entry web portal (in England and Wales) or equivalent mirror eCRF database for Scotland and Northern Ireland, and on to the secure trial randomisation system. Submitted data will be reviewed for completeness and consistency by authorised users within the study group. Submitted data will be stored securely against unauthorised manipulation and accidental loss since only authorised users at site, the Sponsor organisation, Queen Mary University of London or NELA (host of the data entry portal) will have access. Desktop security is maintained through user names and passwords. Data back-up procedures are in place. Storage and handling of confidential trial data and documents will be in accordance with the Data Protection Act 2018 (UK) and General Data Protection Regulation.

### **10.3 Archiving**

Each site will maintain and securely store an investigator site file. NELA and the PCTU (QMUL) will be responsible for archiving identifiable data. Data will be archived in accordance with local standards and procedures for quality and assurance. All other trial documentation and data will be archived by the Sponsor and PCTU in a purpose designed archive facility for twenty years in accordance with regulatory requirements. Access to these archives will be restricted to authorised personnel. Electronic data sets will be stored indefinitely.

### **10.4 Patient identifiable data**

To facilitate linkage to national databases for the collection of follow-up data, patient identifiable data will be collected and entered on to the secure NELA data entry web portal and the randomisation system. Data will be stored and handled in accordance with the Data Protection Act 2018 (UK) and General Data Protection Regulation or equivalent legislation for a particular country or site. In the event that patient identifiable data needs to be transferred between authorised users, this will occur by email [contact] [contact].

## **11 PRODUCTS, DEVICES AND TECHNIQUES**

### **11.1 Cardiac output-guided haemodynamic therapy**

Cardiac output monitors are routinely used in secondary care. Investigators may only use commercially available cardiac output monitoring equipment shown to accurately track changes in cardiac stroke volume, from a list of devices in the intervention SOP. Please see the study intervention SOP for specific details of the intervention.

## **12 SAFETY REPORTING**

### **12.1 Adverse Events (AE)**

An AE is any untoward medical occurrence in a subject to whom an intervention has been administered, including occurrences which are not necessarily caused by or related to that intervention. An AE can therefore be any unfavourable and unintended sign (including an abnormal laboratory finding), symptom or disease temporarily associated with study activities. However, FLO-ELA is a non-CTIMP trial, and all trial interventions are already in routine clinical use for patients undergoing emergency laparotomy surgery. Furthermore, adverse events are very common following emergency laparotomy. AEs will therefore not be collected for the FLO-ELA trial. The DMEC will monitor the safety of the intervention by reviewing in-hospital mortality rates and reported SAEs at intervals in both trial groups.

## **12.2 Serious Adverse Event (SAE)**

A serious adverse event (SAE) is defined as an untoward occurrence that:

- (a) results in death;
- (b) is life-threatening;
- (c) requires hospitalisation or prolongation of existing hospitalisation;
- (d) results in persistent or significant disability or incapacity;

An SAE occurring to a research participant should be reported to the sponsor where in the opinion of the Principal Investigator the event was:

- Related – that is, it resulted from administration of any of the research procedures, and
- Unexpected – that is, the type of event is not listed in the protocol as an expected occurrence.

The FLO-ELA trial is an investigation of a perioperative intervention. It is expected that patients undergoing emergency laparotomy surgery will suffer medical complications, with consequences up to and including death. Only complications considered by the local PI or delegated authority (blinded to study group allocation) to be *related to the use of study procedures* and not a typical complication of emergency bowel surgery should be reported as SAEs. Typical complications of emergency bowel surgery, which should not be reported as SAEs, are included in Appendix 4.

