## 7.5 Intervention algorithm

### General haemodynamic measures (all patients)

1. Maintenance fluid (see SOP) at 1 ml/kg/hr
2. Transfuse blood to maintain haemoglobin >80 g/l
3. Clinician retains discretion to adjust therapy if concerned about risks of hypovolaemia or fluid overload
4. Mean arterial pressure 60-100 mmHg; SpO2 ≥94%; temperature 36.5-37.5°C; heart rate <100 bpm

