### **14.3 *Data monitoring and ethics committee***

The Data Monitoring and Ethics Committee (DMEC) has been formed in accordance with NIHR guidance. It is independent of the trial team and comprises of two clinicians with experience in undertaking clinical trials and a statistician. The committee will agree conduct and remit, which will include the early termination process. During the period of recruitment into the trial the DMEC will monitor safety data and routinely meet to assess safety analyses. The trial will be terminated early if there is evidence of harm in the intervention group or if recruitment is futile. The DMEC functions primarily as a check for safety by reviewing SAEs and in-hospital mortality.

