#### **Appendix 4 – Typical complications of emergency laparotomy**

The following are recognised complications of emergency laparotomy surgery, which may have clinical severity up to and including disability and death.

Acute kidney injury  
Acute Respiratory Distress Syndrome (ARDS)  
Anaphylaxis  
Anastamotic breakdown  
Bowel infarction  
Cardiac arrhythmia  
Cardiac arrest  
Cardiogenic pulmonary oedema  
Deep vein thrombosis  
Delirium or acute psychosis  
Electrolyte imbalance  
Gastrointestinal or other postoperative bleed  
Infection, source uncertain  
Laboratory confirmed bloodstream infection  
Multi-organ dysfunction syndrome  
Myocardial infarction  
Myocardial injury after non-cardiac surgery  
Pneumonia  
Paralytic ileus  
Perforated viscus  
Postoperative haemorrhage  
Pulmonary embolism  
Stroke  
Surgical site infection (superficial, deep or organ/space)  
Urinary tract infection

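### Complications on the Appendix 4 list are exempt from SAE reporting even when judged related, so non-fatal harm of that kind would show only indirectly

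*Combined protocol and SAP*

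**What the plan says.** **Collection.** Section 12.1 states: "AEs will therefore not be collected for the FLO-ELA trial". Its reasons are that the trial is a non-CTIMP, that the interventions are already in routine use, and that adverse events are very common after this surgery.

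**Reporting filter.** Section 12.2 sets two conditions. The event must be judged related to study procedures, "and not a typical complication of emergency bowel surgery should be reported as SAEs". It then says: "Typical complications of emergency bowel surgery, which should not be reported as SAEs, are included in Appendix 4". Appendix 4 covers events of any severity, including fatal ones. Among its entries are "Cardiogenic pulmonary oedema", ARDS, acute kidney injury and cardiac arrhythmia.

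**Recognised risk.** Among the general measures in section 7.5 is: "Clinician retains discretion to adjust therapy if concerned about risks of hypovolaemia or fluid overload". Section 7.4.2 makes the same allowance in the intervention arm.

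**What the DMEC sees.** Section 12.1: "The DMEC will monitor the safety of the intervention by reviewing in-hospital mortality rates and reported SAEs at intervals in both trial groups". Section 14.3: "The DMEC functions primarily as a check for safety by reviewing SAEs and in-hospital mortality". Section 14.3 also says that the trial stops early on evidence of harm in the intervention group, and names no non-fatal measure. Section 7.6 says the committee sees outcome results by treatment group, without saying which outcomes or when.

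**Outcomes.** Sections 5.2, 5.4 and 5.5 list DAOH-90, mortality, hospital stay, critical-care stay and readmission. No complication is listed.

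**The concern.** The intervention is a protocol of repeated fluid challenges, and the protocol itself recognises fluid overload as a concern. Pulmonary oedema is an obvious form that such harm might take, and it is on the exempt list. Because both conditions in 12.2 must be met, a serious non-fatal pulmonary oedema that the investigator attributes to trial fluid is not reported.

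A related-and-unexpected rule is a reasonable filter for rapid reporting to the sponsor and ethics committee under 12.3. The difficulty is that the same filtered stream is the only non-fatal safety input that 12.1 and 14.3 name for the DMEC. At stake is whether the committee, and later the final report, can describe non-fatal harm by arm in a trial that also enrols patients without capacity on a stated basis of negligible risk (7.1).

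**Working it through.** **1. Follow one event through the text.** Take a non-fatal cardiogenic pulmonary oedema judged related to study procedures.

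- 12.1: not recorded as an AE, because none are collected.
- 12.2: meets the first condition (related) and fails the second (it is a listed complication), so it is not reported as an SAE.
- 12.1 and 14.3: it is absent from the SAE stream and from in-hospital mortality.
- 5.2 to 5.5: it counts only if it lengthens hospital or critical-care stay or leads to readmission.
- 7.6: it reaches the DMEC only if the outcome results shown by arm include those measures.

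The exemption is not complete. Fluid overload as such and abdominal compartment syndrome are not in Appendix 4, so a related serious case of either could be reported.

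**2. Reproduce the plan's sample size, to fix the variance and n.** Inputs from 8.1: difference 3.2 days, SDs 28.0 and 27.1, 90% power, 5% alpha, 2% dropout; 8.2 makes the test two-sided.

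- Pooled SD = √((28.0² + 27.1²)/2) = 27.55.
- n per arm = 2 × 27.55² × (1.960 + 1.282)² / 3.2² = 1559; divided by 0.98 = 1591, or 3182 in total. The plan has 3138, a difference of 1.4%, so it reproduces.
- Analysed per arm: 1569 × 0.98 ≈ 1538.
- Standard error of the DAOH-90 difference = 27.55 × √(2/1538) ≈ 0.99 days.

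**3. How much would DAOH-90 reveal?** The documents give no complication rates and no days lost per complication, so both are assumptions shown over a range. The shift in mean DAOH-90 is (excess risk) × (days lost per case). Power in the harm direction is Φ(shift/0.99 − 1.96), which is 2.5% when there is no harm. The direct count is a two-sided 5% comparison of two proportions. Days lost are 3 to 10 per case, and the complication is assumed not to cause death.

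| Usual care → intervention | Extra cases | DAOH-90 shift (days) | Power, DAOH-90 | Power, direct count |
|---|---|---|---|---|
| 2% → 3% | 15 | 0.03–0.10 | 3% | 43% |
| 2% → 4% | 31 | 0.06–0.20 | 3–4% | 90% |
| 5% → 7.5% | 38 | 0.08–0.25 | 3–4% | 82% |
| 5% → 10% | 77 | 0.15–0.50 | 4–7% | >99% |
| 10% → 15% | 77 | 0.15–0.50 | 4–7% | 99% |
| 10% → 20% | 154 | 0.30–1.0 | 5–17% | >99% |

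The last column applies to a field that records the complication itself. It is not the power of any existing NELA field.

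**4. What is already collected.** In Appendix 2, data field 7.5 (unplanned step-up from the ward in the first week), fields 7.4 and 7.4a (return to theatre and the reason for an unplanned one) and field 7.1 (critical-care days) are not marked as withheld from the trial. Field 7.1 already feeds a process measure (5.5, 5.7). The others are not named as outcomes or as DMEC data.

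**The case against.** The strongest case for the plan is that 12.1 gives reasons for the choice. Background complications are frequent and the treatment is in routine use, so reporting every listed event would bury any signal. That stands as a defence of Appendix 4 for expedited reporting. It does not explain why listed events judged related should be uncounted altogether.

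Several stronger readings are tempting, and the documents do not support them:

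- *The DMEC reviews nothing but deaths and SAEs.* Section 14.3 says primarily and lets the committee agree its remit, and 7.6 gives it outcome results by arm. SAP V4.0, cited in section 8, and any DMEC charter are not in the text reviewed and may say more.
- *Non-fatal harm cannot be seen.* DAOH-90, hospital stay, critical-care stay and readmission are all compared by arm, so harm that prolongs care can appear there, diluted and unattributed.
- *Stopping for harm rests on in-hospital death alone.* That overlooks 7.6 and the unlisted events that remain reportable.
- *The list exempts every harm of fluid.* Fluid overload and abdominal compartment syndrome are unlisted. The documents name fluid overload as a concern but do not tie particular Appendix 4 entries to the intervention; that link is a clinical inference.

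The substitute fields are also imperfect. Field 7.5 leaves out step-ups from HDU, PACU or enhanced-care areas, which is where much of the postoperative intervention is delivered (7.4.2). Field 7.1 leaves out PACU stay. Field 7.4 changed on 1/12/2019. These objections limit what the fields can show, but they do not remove the gap. Vasopressor and inotrope use would be a poor addition, because it records treatment given rather than harm.

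**Conclusion.** The point holds in a limited form. A related complication on the Appendix 4 list is not reported as an SAE, and no planned by-arm count of complications replaces it. Non-fatal harm of that kind would therefore be visible only indirectly. Over the assumed range (usual-care rates 2 to 10%, risk ratios 1.5 to 2.0, 3 to 10 days lost per case), DAOH-90 would move by 0.03 to 1.0 days with 3 to 17% power, against 43% to over 99% for a direct count. Those figures show how weak DAOH-90 is as a safety signal. They do not estimate any actual harm, and they were not worked out for critical-care stay or readmission.

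Sections 7.6, 12.1 and 14.3 also describe the DMEC's inputs differently and need reconciling. None of this affects the primary analysis. It is an inexpensive improvement to safety reporting, and the conclusion assumes that SAP V4.0 and any DMEC charter do not already provide it.

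**What to change.** 1. **By-arm tabulation.** In 12.1 and 14.3, add Appendix 2 fields 7.5, 7.4/7.4a and 7.1 to the DMEC closed report. Add 7.5 and 7.4/7.4a to the final safety table (critical-care days are already reported as a process measure). For 7.4, use only whether there was any unplanned return, since the question covered unplanned returns alone before 1/12/2019. Footnote the limits of 7.5 and 7.1, and note that participants whose procedure falls outside NELA have their NELA data removed (7.10).
2. **Listed events judged related.** Keep Appendix 4 as the filter for expedited SAE reporting. Reconcile 12.2 with the evidence-of-harm rule in 14.3 so that these events are at least counted for the DMEC. Relatedness is judged by an investigator described as blinded (7.6, 12.2), so these counts should be read beside the tabulation in (1), which needs no attribution.
3. **DMEC inputs.** Reconcile 7.6, 12.1 and 14.3 on which outcomes the committee sees by arm, and when.

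Item 1 needs no new data, only extra tables. Item 2 adds some event records; the documents give no basis for estimating how many. Recruitment status is not stated. With a proposed end of 31 January 2026 and one-year follow-up for the last patient (7.11), recruitment would close by about January 2025. If it has closed, the final safety table is the useful part. No treatment rule changes.

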## **12.3 Notification and reporting of Serious Adverse Events**

Serious Adverse Event (SAEs) that are considered to be 'related' and 'unexpected' are to be reported to the sponsor and the sponsor's representative within 24 hours of learning of the event. The event will be reviewed by the CI and if it meets the criteria for an SAE, will then be reported to the REC within 15 days of receipt of the SAE report.

